### Enrolment of participants

HFSs will be conducted during the first trimester of 2025. Children aged 2–10 years with fever or history of fever (table 3) will be screened using routine HRP2-based RDTs (First Response Malaria Antigen *P. falciparum* HRP2 [Premier Medical] or SD Bioline Malaria Ag Pf, 05FK50 [Abbott,] depending on national procurement at the time of the study) and an additional confirmatory RDT targeting *P. falciparum* LDH (Biocredit Malaria AG Pf (pLDH) C14RHG25, Rapigen) selected from the recommended options in the WHO master protocol.^33^ Assuming that 85% of samples will be of high sequencing quality, the sample size per health facility will be increased from 60 to 71. Dried blood spots will be collected from study participants if either test is positive, and samples with discrepant RDT results will be used to detect *pfhrp2/3* deletions. The number of people to be screened at each health facility and the duration of recruitment to achieve the sample size will depend on the RDT positivity rate among study participants meeting the eligibility criteria.

**Table 3 T3:** Study eligibility criteria

Inclusion criteria	Exclusion criteria
Children aged 2–10 years of age (cluster sampling). >6 months of age (dense sampling).	Any symptoms of severe malaria.
Fever (axillary temperature≥37.5°C) or history of fever in the preceding 24 hours.	
At least one positive parasitological test for malaria diagnosis via RDT*.	Negative parasitological test for malaria via RDT (except any women at their first ANC visit, who will be recruited before testing for malaria with an RDT).
OR	
Pregnant women (≥12 years of age) attending first antenatal care visit.	Unwilling to provide informed, written consent.
AND	
Informed, written consent to participate from participant and/or guardian.	History of antimalarial treatment in the last 14 days

* Routine one (First Response Malaria Antigen HRP2 [Premier Medical Inc] or Bioline Malaria Ag Pf, 05FK50 [Abbott], depending on national procurement at the tiem of the study) plus a second RDT (BIOCREDIT Malaria Ag pLDH), the latter being provided to support detection of deletions.Routine RDT (First Response® Malaria Antigen *P. falciparum* HRP2 [Premier Medical Inc] or SD Bioline Malaria Ag Pf [Abbott, 05FK50], depending on national procurement at the time of the study) plus a second confirmatory RDT (BIOCREDIT Malaria Ag Pf pLDH, Rapigen Inc), the latter being provided to support detection of *P. falciparum* parasites with *pfhrp2* deletions

ANCantenatal careRDTrapid diagnostic test

Women attending their first ANC visit (table 3) will be invited to participate in the study (if they live in the study area) by trained nurses, who will assign a unique identification number to consenting and eligible women and complete a brief form including date of visit, mother’s age, gravidity, week of pregnancy, area of residence and recent or past movements. Women will also be asked about health-seeking behaviours and use of interventions. Finally, women will be finger pricked for malaria RDT along with routine tests, treated if positive and a dried blood spot collected on filter paper for molecular analysis.

Dense sampling in Magude, Matutuine and Namaacha districts will be coordinated with district malaria focal points, community health workers (CHW), malaria volunteers (who provide a link between the CHW and the health facility, and assist the CHW in the follow-up of cases and administration of medication) and health facilities. All *P. falciparum* positive RDTs (SD Bioline Malaria Ag Pf, 05FK50, Abbott) among clinical cases (>6 months old; table 3) will be stored for molecular analysis. Once a case is notified, field workers will travel to the household of the case to collect Global Positioning System location within the period of 3 days (up to 7 days if needed).

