## Methods and analysis

### Study design and sample size calculations

This is a prospective genomic surveillance study of *P. falciparum* samples to be collected between 2024 and 2026 from a variety of transmission intensities and geographies in Mozambique. Sampling design and efforts will be driven by target use cases. A multicluster probabilistic health facility sampling (HFS) sampling scheme^31^ will be followed to detect *pfhrp2/3* deletions and markers of antimalarial resistance across the 10 country provinces (figure 2A). Dried blood spots will be collected from a consecutive sampling of 60 RDT-confirmed malaria clinical cases per health facility, from a systematic random sample of four health facilities per province (figure 2B and table 1). Using the DRpower tool and associated web-based *pfhrp2/3* Planner,^32^ the study power was estimated to detect the prevalence of *hrp2/3* deletions above the 5% threshold at the regional level.^33^ Assuming an intracluster correlation coefficient (ICC) of 0.05 based on historical data (https://mrc-ide.github.io/DRpower/articles/historical_analysis.html), power was estimated at 92.4% (91.9%–92.9%) in regions with three provinces (12 clusters of 60 samples) and 96.9% (96.5–97.2%) in regions with four provinces (16 clusters of 60 samples). Power remains high under the more pessimistic assumption of ICC=0.1, being 78.6% (77.8%–79.4%) and 86.3% (85.6%–87%) for regions with 3 and 4 provinces, respectively. This same design will be used to estimate the prevalence of *pfdhps* mutations at codon 540 at the province level (margin of error analysis). Assuming a mutation prevalence of 90%,^34^ prevalence will be estimated to within 4.8% margin of error for ICC=0.01 and within 7.5% margin of error for ICC 0.05^31^ (assuming lower ICC than for *pfhrp2/3* given the lower variance between clusters expected when looking at smaller geographic scale). Finally, the design will be used to detect the presence of variants of concern (VOCs), namely *pfkelch13* markers of artemisinin partial resistance and *pfdhps-*581 marker of SP resistance, at the province level (presence/absence analysis). Assuming VOCs at 1% prevalence in the population, the design has 85% power to detect VOCs if ICC=0.01 and 67% if ICC=0.05^31^.

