### Study outcomes and analysis plan

This project has six primary endpoints. First, prevalence of drug-resistance markers at individual codons, or multicodon haplotypes if successfully phased, will be calculated at provincial level as the number of samples carrying a mutant allele or haplotype out of all samples with a valid genotype for the respective locus. Differences in the prevalence of drug resistance markers (1) between provinces; (2) between years and (3) after interventions will be evaluated using Fisher’s exact test. If emerging VOCs are identified, genetic relatedness between infections will be assessed to describe potential sources and origins of the variants. Allele frequencies will be estimated using methods that account for sample polyclonality.^45^

Second, the prevalence of suspected false-negative HRP2-RDT results among symptomatic patients with *P. falciparum* malaria will be determined at the regional level using the DRpower tool, which accounts for intracluster correlation when estimating the prevalence.^32^ The prevalence of false-negative HRP2-RDT caused by *pfhrp2/3* deletions will be determined as the number of *pfhrp2* or *pfhrp3* deletions confirmed by qPCR^40^ divided by the total number of confirmed cases in a given region.

Third, sources of importation and transmission will be identified using genetic relatedness (identity-by-descent [IBD]) between pairs of samples estimated using Dcifer software.^46^ The fraction of highly related pairs (using a threshold in IBD) will be calculated for samples within each province and between different provinces to characterise the spatial connectivity of parasite genetic populations. Isolation-by-distance will be calculated to assess the extent to which genetic relatedness decreases with geographic distance. Cases from areas targeted for elimination will be classified as local or imported infections by combining data on participants’ reported travel (dates and duration of travel), epidemiologic data from source and destination areas (malaria incidence estimated from DHIS2 data) and genetic data from source and destination areas (relatedness of samples via IBD). Outbreaks will be detected in the study areas using EpiFRIenDs software,^20^ and genetic relatedness analysis within outbreaks will be performed to quantify the number of transmission events causing the outbreak.

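### The confirmed-deletion proportion is biased low if the pLDH test misses infections that HRP2 finds, and the printed power shows no allowance for this

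*Protocol article*

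**What the plan says.** In the Protocol article, *Enrolment of participants*, febrile children aged 2–10 years are screened with a routine HRP2 test and an additional pLDH test. The enrolment rule is "Dried blood spots will be collected from study participants if either test is positive", and the eligibility table likewise asks for "At least one positive parasitological test for malaria diagnosis via RDT". On finding pfhrp2/3 deletions, the same section states that "samples with discrepant RDT results will be used to detect" them.

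*Study outcomes and analysis plan* (second primary endpoint) names two quantities:

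- The prevalence of suspected false-negative HRP2 results among symptomatic patients with *P. falciparum* malaria, estimated by region with DRpower.
- The prevalence of false negatives caused by deletions: the count of qPCR-confirmed deletions in either gene, "divided by the total number of confirmed cases in a given region".

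*Study design and sample size calculations* gives the power to detect "deletions above the 5% threshold at the regional level". The base case takes its ICC of 0.05 from past surveys. For a three-province region the section reports "power was estimated at 92.4% (91.9%–92.9%) in regions with three provinces (12 clusters of 60 samples". A four-province region, which has 16 clusters of the same size, is given 96.9%. At ICC 0.1 the figures are 78.6% and 86.3%. The *Discussion* repeats them as above 92% and above 78%. The true prevalence at which power was computed is not printed, nor is the sensitivity of either test.

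**The concern.** The two kinds of infection do not have the same chance of entering the survey. An infection whose HRP2 test is negative because of a deletion is sampled only if pLDH is positive. Any other infection is sampled if HRP2 or pLDH is positive. HRP2-positive/pLDH-negative cases therefore take up places among the 60 per facility, while their deletion-carrying counterparts, missed by pLDH, are never sampled. Perfect qPCR typing of everyone enrolled would not repair this, because the missing infections leave no specimen.

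The error in the confirmed-deletion proportion has one direction. It can hide a region that is above the 5% threshold but cannot create one. Hiding such a region is the failure that this endpoint is meant to prevent.

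**Working it through.** **Inputs from the Protocol article.** 12 or 16 clusters of 60; ICC 0.05 or 0.1; threshold 5%; either-positive enrolment; 71 enrolled per facility to allow for 85% sequencing quality (60/0.85 = 70.6).

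**Assumptions, because the article does not give them.** True prevalence π = 10%; uniform prior on prevalence; Beta(1,9) prior on ICC; a region is declared above 5% when the posterior probability exceeds 0.95; test sensitivities.

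**Step 1: reproduce the printed power.** Beta-binomial clusters, every infection equally likely to enter, 8,000 simulated surveys per cell:

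| Clusters | ICC | Printed | Simulated at π = 10% |
|---|---|---|---|
| 12 | 0.05 | 92.4% | 92.0% |
| 16 | 0.05 | 96.9% | 96.7% |
| 12 | 0.1 | 78.6% | 78.9% |
| 16 | 0.1 | 86.3% | 86.5% |

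With equal entry, prevalences of 8, 9, 11 and 12% do not fit: at 12 clusters and ICC 0.05 they give 66.5, 83.5, 96.8 and 99.1%.

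**Step 2: the bias.** Let sL be the probability that pLDH is positive, sE the probability that at least one test is positive in an infection HRP2 can detect, and r = sL/sE. Either-positive includes pLDH-positive, so r ≤ 1 when pLDH performs equally in both groups. The expected confirmed proportion is

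π·sL / (π·sL + (1 − π)·sE) = πr / (πr + 1 − π).

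At π = 0.10 and r = 0.80 this is 0.08/0.98 = 8.2%.

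**Step 3: the power.** Selection acts within each facility, so each cluster prevalence t becomes tr/(tr + 1 − t). This also narrows the spread between clusters. At π = 10%, 60 per cluster:

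| r | Expected proportion | ICC 0.05, 12 / 16 clusters | ICC 0.1, 12 / 16 clusters |
|---|---|---|---|
| 1.00 | 10.0% | 92.0 / 96.7% | 78.9 / 86.5% |
| 0.97 | 9.7% | 90.7 / 95.7% | 76.7 / 84.7% |
| 0.95 | 9.5% | 89.4 / 94.9% | 74.9 / 83.6% |
| 0.90 | 9.1% | 85.7 / 92.0% | 70.2 / 79.4% |
| 0.80 | 8.2% | 74.8 / 83.0% | 59.5 / 68.2% |
| 0.70 | 7.2% | 57.5 / 65.2% | 45.8 / 52.5% |

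**Step 4: what r could be.** With independent test errors, r = sL/[1 − (1 − sL)(1 − sH)], where sH is HRP2 sensitivity in infections without a deletion. Over sH = 0.80–0.99, r is about 0.98 for sL = 0.98, 0.95–0.96 for 0.95, 0.90–0.92 for 0.90 and 0.80–0.83 for 0.80. If pLDH finds everything HRP2 finds, r = 1.

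**Step 5: the two series under the two denominators.** Take π = 10%, sL = sH = 0.95 and independent errors.

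- Either-positive: 0.10 × 0.95 + 0.90 × 0.9975 = 0.99275. pLDH-positive: 0.95.
- Confirmed deletions: 0.10 × 0.95 = 0.095.
- Suspected false negatives: 0.095 + 0.90 × 0.05 × 0.95 = 0.13775.

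| Series | Over either-positive | Over pLDH-positive |
|---|---|---|
| Confirmed | 9.6% | 10.0% |
| Suspected | 13.9% | 14.5% |

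The pLDH-positive denominator removes the bias in the confirmed series. The suspected series is too high under both. With no deletions at all it would read 0.0475/0.9975 = 4.8% and 0.0475/0.95 = 5.0%.

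**Step 6: cost of the pLDH-positive denominator.** The share of enrolled cases kept is r/(πr + 1 − π). At r = 0.80 this is 0.80/0.98 = 0.816, so 60 becomes 49 and 71 becomes 58. Simulated at ICC 0.05 over r = 0.95 to 0.70, power is about 90–92% (12 clusters) and 95–97% (16 clusters) starting from 60. It is about 92–93% and 96–97% if all 71 can be used.

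**The case against.** **A reader might infer that the printed 92–97% power is not delivered.** The documents do not support that. The loss depends on r, which they do not give. It is nil at r = 1 and under 2 points at r ≥ 0.97.

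**A reader might infer that every deletion-carrying infection must enter through pLDH.** It need not. The endpoint counts pfhrp2 or pfhrp3 deletions, and the plan recognises polyclonal infections. A pfhrp3-only deletion, or a deleted clone mixed with an intact one, can be HRP2-positive. The argument covers only infections that are HRP2-negative because of a deletion.

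**A reader might infer that the endpoint always errs low.** The series assigned to DRpower is the suspected one, which includes HRP2 false negatives without a deletion and errs upward (Step 5). That upward error does not correct the confirmed proportion, which is the quantity the power statement describes.

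**The strongest objection concerns the estimand.** If the target is prevalence among test-confirmed cases, and the unprinted alternative was set on that scale, the printed power stands. The article does not define a confirmed case, and the full protocol or the cited master protocol may fix the denominator. This objection has force. But the article also describes the target population as symptomatic patients with *P. falciparum* malaria, and on that reading the shortfall is real. Either way, the reader cannot tell which prevalence the power refers to.

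**Conclusion.** The point holds in a limited form. For infections made HRP2-negative by a deletion, either-positive enrolment pulls the qPCR-confirmed proportion below the true prevalence among infections whenever pLDH misses infections that HRP2 detects. The article shows no allowance for this. At an assumed true prevalence of 10% and ICC 0.05, the loss is about 1 point at r = 0.97, 2–3 at 0.95, 5–6 at 0.90, 14–17 at 0.80 and over 30 at 0.70.

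This rests on four assumptions: the 10% alternative, the simulated decision rule, the range for r, and equal pLDH sensitivity in infections with and without a deletion. It is a worthwhile, inexpensive improvement and does not show that the survey is underpowered.

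**What to change.** 1. For the regional 5% decision on deletions, apply DRpower per facility to qPCR-confirmed deletions among HRP2-negative/pLDH-positive cases, over all pLDH-positive cases. Both kinds of infection then pass the same entry test.
2. Report the proportion over all either-positive cases alongside, for comparability.
3. Do not use the suspected, unconfirmed series for that decision. A pLDH-positive denominator does not cure its upward error. It can still be reported as a description of suspected false negatives.
4. In *Study design and sample size calculations* and in the *Discussion*, state the assumed true prevalence, and that the printed power assumes equal ascertainment of HRP2-negative and HRP2-positive infections.

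No new sampling is needed. Both test results must already be known for enrolled children, because discrepant samples are selected on them. The downside is that HRP2-positive/pLDH-negative cases leave the denominator, which costs about 1–2 points of power.

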### Data and sample collection

Field workers and nurses will be trained to ask for informed consent, perform a simple questionnaire and collect biological samples for molecular analysis.^4^ The survey questionnaire will be administered to all study participants or children’s parents/guardians meeting the inclusion criteria and will include characteristics of the participant and malaria related information. Nurses will be trained to collect blood by finger pricking following standard procedures.^4^ For each participant, either the *P. falciparum*-positive RDT used for routine malaria diagnosis (dense sampling scheme) or four blood spots onto two filter papers (Whatman 3 MM; all other sampling schemes) will be collected. Specimens will be labelled anonymously (patient unique identifier, study health facility and date), dried for 24 hours and kept in individual plastic bags with desiccants at 4°C. Every 2–6 weeks, the informed consents and samples will be sent to Centro de Investigação em Saúde de Manhiça (CISM) through a local transportation agency. A data manager will be responsible for the receipt of the informed consents, and a laboratory technician will be responsible for receiving the samples and storing them at −20°C until analysis. Part of the dried blood spot will be stored in RNA-preserving solution for future transcriptional studies. All samples will be kept in the CISM Laboratory for a period of approximately 15 years.

### Molecular analyses

We will genotype samples using targeted amplicon sequencing to characterise sequence (single-nucleotide polymorphisms [SNP], microhaplotypes and haplotypes) and copy number (duplications and deletions) variants. We will use the MAD^4^HatTeR targeted sequencing panels (developed at EPPIcenter—UCSF and Paragon Genomics, California, USA) on approximately 7690 *P*. *falciparum* samples (based on expected positivity rates). MAD^4^HatTeR is a modular assay that targets up to 239 *P*. *falciparum* amplicons of ≈250 bp, which include microhaplotypes informative about genomic diversity and relatedness in Africa,^19 35^ targets for *pfhrp2/3* deletions,^6 7^
*pfcsp* polymorphisms encompassing the TH2R and TH3R epitopes included in the R21/Matrix-M^23^ and RTS,S vaccine^28^ and drug resistance markers in 13 genes,^34^ including polymorphisms associated with resistance to artemisinin (*pfkelch13*),^36^ SP (*pfdhfr* and *pfdhps*),^37^ chloroquine (*pfcrt*^38^) and amodiaquine (*pfcrt* and *pfmdr1*). Additionally, targets for four non-*falciparum* species detection are included. Targeted amplicons obtained by PCR on genomic DNA using Illumina-specific adaptors and sample-specific barcode will be pooled to create a single product library, which will be sequenced (paired end 150 bp) on a MiSeq Illumina sequencer at CISM or higher performance equipment when available. We will use qPCR to determine parasite density,^39^ confirm *pfhrp2/3* deletions,^40^
*Plasmodium* species^41 42^ and copy-number variants (CNVs) in markers of piperaquine and mefloquine resistance (*pfpm2* and *pfmdr1*).^43^ We will also perform whole-genome sequence a subset of *P. falciparum* samples to generate a longitudinal catalogue of generate a longitudinal catalogue of genome-wide variations.

### Bioinformatic analysis

To infer alleles, FASTQ files from amplicon sequencing will be run through a Nextflow-based pipeline developed and benchmarked for data generated with MAD^4^HatTeR (https://github.com/EPPIcenter/mad4hatter). Briefly, primer dimers will be removed, and reads will be demultiplexed for each target, filtered based on quality and length, clustered using an error-inference model and aligned to the reference genome to remove non-specific amplification. To remove spurious variants in error-prone sequences, homopolymers and tandem repeats will be masked. Subsequently, low-abundance alleles (fewer reads than the maximum observed in negative controls or with within-sample allele frequency<1%), and samples with low target coverage (<50 targets for genetic diversity and relatedness with a read depth of>100) will be removed.^19^ Multilocus markers will be analysed using downstream modules for SNP phasing and multilocus allele frequency inference algorithms currently under development and benchmarking. We will identify putative CNVs using a generalised additive model to normalise read depth and calculate fold change across several targets for each gene of interest (*pfpm2* and *pfmdr1*). Putative CNVs will be confirmed by qPCR.^43^

### Quality control and assurance

The questionnaires will be administered to study participants using a Redcap tablet by public health technicians assigned to the health facilities by the Ministry of Health. At each site, a local supervisor will conduct a thorough review of the information before it is sent weekly to the data centre at the CISM. A quality control of the collected data will be performed weekly by data managers and research assistants, who interact with the local supervisors to correct possible errors.

A quality control programme for molecular determinations will be followed using an artificial set of controls with known genotypes (laboratory clones in monoclonal and polyclonal mixtures at different proportions and parasite densities). In addition, the team will participate in the WHO/United Kingdom National External Quality Assessment Service (UK NEQAS) scheme for molecular assays for *Plasmodium* species identification and *pfhrp2/3* gene deletion detection.

### Data management

Patient data will be collected using password-protected electronic devices. Automated quality checks will be performed to ensure data completeness. Confidentiality and security will be ensured through automatic encryption of sensitive data, storage on password-protected computers and in secured locations and data sharing using password-protected, encrypted files. Data will be deidentified prior to analysis, with the exception of geolocation codes required for spatial analyses. The study will also use data available from the NMCP, including District Health Information System V.2 (DHIS2) incidence data, intervention coverage, historical prevalence surveys, travel history or other mobility assessments and entomological data. Sequences generated from sample analysis will be integrated into a curated catalogue of genomic data, together with relevant anonymised clinical and epidemiological information, and made publicly available in public repositories such as the Sequence Read Archive (SRA, National Center for Biotechnology Information [NCBI]) or the European Nucleotide Archive, as well as the MalariaGEN Resource Center. To facilitate data accessibility and use by the NMCP and to achieve meaningful integration with other sources of surveillance data, genetic information will be incorporated into the DHIS2-based Integrated Malaria Information Storage System (iMISS), which is currently being implemented in Mozambique^44^ (figure 3).

